# An evaluation of Croí MyAction community lifestyle modification programme compared to standard care to reduce progression to diabetes/pre-diabetes in women with prior gestational diabetes mellitus (GDM): study protocol for a randomised controlled trial

**DOI:** 10.1186/1745-6215-14-121

**Published:** 2013-05-02

**Keywords:** Gestational diabetes mellitus, Pre-diabetes, Risk factor modification, Lifestyle intervention, Interdisciplinary approach, Randomised controlled trial

## Abstract

**Background:**

Universal screening using the International Association of Diabetes and Pregnancy Study Groups (IADPSG) criteria has identified a prevalence of gestational diabetes mellitus (GDM) of 12.4% in women living in Ireland. Women with prior GDM are at increased risk of developing type 2 diabetes later in life. A number of risk factors linked to the development of type 2 diabetes are potentially modifiable through lifestyle and behaviour changes, and medical management. No previous Irish studies have adequately investigated the efficacy of lifestyle intervention programmes in reducing these risk factors in women with prior GDM. Through a two-group, parallel randomised controlled trial (RCT), this study aims to assess the clinical impact, cost-effectiveness and psychological experience of the Croí MyAction intensive lifestyle modification programme for women with prior GDM.

**Methods/Design:**

A total of 54 women with a history of GDM and persistent post-partum glucose dysfunction (impaired glucose tolerance (IGT) or impaired fasting glucose (IFG)), are randomly assigned to a control arm (n = 27) or to the Croí MyAction intervention group (n = 27). The control arm receives usual health care advice - written information on diet and lifestyle changes for reducing diabetes risks and visits with general practitioners as required. The intervention group receives usual health care as per the control group in addition to attending a 12-week intensive lifestyle modification programme known as Croí MyAction. Croí MyAction involves 2.5 hour sessions once per week (for 12 weeks) comprising a group exercise programme, group health promotion or education seminars, and one-to-one meetings with a multidisciplinary health care team to personalise risk factor reductions. Randomisation and allocation to the intervention arms is carried out by an independent researcher, ensuring that the allocation sequence is concealed from study researchers until the interventions are assigned. The primary analysis is based on glucose dysfunction, comparing a mean reduction in fasting plasma glucose (FPG) levels on a 75 gram oral glucose tolerance test (OGTT) in the two groups at a one-year, post-intervention follow-up. The trial is funded by the Irish Health Research Board (HRB). Ethics approval was obtained on 27 March 2012 from the Clinical Research Ethics Committee, Galway University Hospitals, Health Service Executive of Ireland (Ref: C.A.691).

**Trial registration:**

Current Controlled Trials ISRCTN41202110.

## Background

Gestational diabetes mellitus (GDM) is defined as any degree of glucose intolerance resulting in hyperglycaemia, or excess sugar, in a mother’s blood during pregnancy [1]. When present, the pregnancy may be associated with a number of adverse maternal and neonatal outcomes. Neonatal complications include hypoglycaemia respiratory distress syndrome and jaundice, and macrosomia may result in shoulder dystocia [2-5]. Adverse maternal outcomes include pregnancy induced hypertension (PIH), pre-eclampsia toxaemia (PET), polyhydramnios and an increased risk of delivery by caesarian section [2,4-6]. GDM is also associated with increased psychological stress during pregnancy [7]. Later in life, both the mother and child are at increased risk of hospital admission, obesity, type 2 diabetes and heart disease [8-14].

There is a paucity of robust evidence relating to the prevalence of GDM in the international literature [15]. Prevalence estimates have been complicated by the wide range of definitions and test criteria used for diagnosing GDM and vary according to region and ethnic group [16]. There is a general consensus, however, that the prevalence of GDM is increasing globally and occurs in approximately 2 to 9% of all pregnancies [6,17]. Several factors have been shown to be associated with an increased risk of GDM. Increasing age, previous GDM, pre-pregnancy obesity, a previous macrosomic baby (larger than 4.5 kg), a family history of diabetes (amongst first-degree relatives), and particular ethnic origins are generally accepted as risk factors [16]. In Ireland, accurate and up-to-date data on the incidence of hyperglycaemia in pregnancy were lacking prior to 2007, when the first results of the Atlantic Diabetes in Pregnancy (DIP) research programme were published. The Atlantic DIP programme, funded between 2005 and 2010 by Ireland’s Health Research Board, found that at least 12% of pregnancies are complicated by GDM in Ireland [3]. In addition, approximately 18% of these women suffered from persistent post-partum glucose abnormalities in the first year following the birth, compared to 2% in women with proven normal glucose tolerance (NGT) in the index pregnancy, during the same time and accessing the same health care services in the same geographical location [13]. These glucose abnormalities included type 2 diabetes, but also IFG, IGT, metabolic syndrome (MetS) and insulin resistance (IR), conditions recognised as intermediary stages in the development of type 2 diabetes.

Diabetes is associated with significant morbidity and mortality and is one of the fastest growing chronic health conditions in Ireland and worldwide. Some of the biological risk factors associated with the development of type 2 diabetes are non-modifiable, such as age, ethnicity or family history of the disease. However, there are a range of risk factors that are potentially modifiable through lifestyle changes, for example, central adiposity, elevated fasting blood sugars, triglycerides or blood pressure; behavioural factors, such as poor diet or sedentary lifestyle; and a host of cognitive and mood factors which delimit or facilitate healthy lifestyle changes (self-efficacy, motivation to change, depression or anxiety) [18]. A growing body of research suggests that “for people with pre-diabetes, weight loss and therefore reduction in body mass index (BMI) and waist circumference [alone] is successful in reducing the risk of developing diabetes” [18]. Saaristo *et al.* (2010) found that modest weight loss (circa 5%) in a community care setting is especially effective in reducing risk of diabetes [19].

With this evidence, randomised clinical trials in a number of countries have investigated the effects of lifestyle interventions in high risk groups, including women with prior GDM, on the reduction of progression to type 2 diabetes [18,20-23]. These studies have shown that type 2 diabetes can be prevented, or at least postponed, by even modest lifestyle changes. In Ireland, no previous research has adequately evaluated the outcomes of lifestyle intervention for this cohort of women. Without such research, we are left with an inadequate analysis of the efficacy of lifestyle intervention programmes for delaying diabetes onset in women with prior GDM in Ireland. It is also unclear whether participation in such interventions can help women sustain improvements in lifestyle practices, such as diet and physical activity, over time (that is, when the intervention is over). This study seeks to remedy this gap through the development of a randomised controlled trial (RCT) which will evaluate the effectiveness of Croí MyAction, an intensive 12-week lifestyle intervention programme, as compared with standard health care provided to women with a history of GDM. The trial will compare the two study arms in terms of a mean reduction in fasting blood glucose dysfunction from the time of a baseline assessment to a one-year follow-up.

Croí is the West of Ireland Cardiac Foundation. Croí MyAction is a lifestyle and risk factor modification intervention programme offered to people at risk of cardiovascular disease. It is the only initiative of its kind in the country that integrates the care of patients at high risk of cardiovascular diseases and type 2 diabetes in a community-based setting. Croí MyAction was developed in collaboration with the Irish Health Service Executive (HSE) and Imperial College London. The 12-week intervention programme is modeled on the European Society of Cardiology demonstration project, a large clinical trial called EuroAction. EuroAction was a cluster RCT of a preventive cardiology intervention programme in Europe. It demonstrated that nurse-managed, multi-disciplinary, family-based programmes could achieve healthier lifestyle changes and better risk factor control than usual care at the time of a one-year follow-up [24]. The 12-week Croí MyAction programme in Ireland incorporates the principles and protocols of EuroAction. It is delivered by a multidisciplinary team of nurses, dieticians, physiotherapists and physical activity specialists, supported by a physician. It is family-centered, encouraging patients to participate in the programme with a partner. The emphasis of Croí MyAction is on healthy lifestyle change aimed at improving quality and enjoyment of life; for example, empowering individuals and families to make sustainable changes through behavioural approaches, such as motivational interviewing and goal-setting. The programme includes management of blood pressure, lipids, glucose and adherence with cardio-protective medications; finally, it is community-based, thus increasing its accessibility.

While this model of prevention has been evaluated through the EuroAction study, it has not been assessed in women with prior GDM. In this study, therefore, the effectiveness of the Croí MyAction programme will be measured in terms of a reduction in the modifiable biomedical, anthropometric and psychosocial risk factors associated with the development of type 2 diabetes in women with prior GDM. In addition, following the RCT, qualitative methods will be used to examine participants’ experiences of the Croí MyAction intervention programme in terms of its feasibility and perceived strengths and weaknesses. Finally, an economic evaluation will be undertaken to explore the cost-effectiveness of the programme. This integrative, multidisciplinary approach - incorporating clinical, psychological and economic evaluations - is expected to make novel contributions to knowledge in the field of diabetes research.

## Methods/Design

### Setting

The study takes place along the Irish Atlantic seaboard, which extends from the north-western corner of Ireland through the west coast and islands, to the city of Galway. The coordinating centre is the School of Medicine at the National University of Ireland, Galway (NUI Galway), involving the academic departments of medicine, obstetrics, general practice, economics and psychology. The intervention programme is delivered by Croí–West of Ireland Cardiac Foundation, a community-based organisation also located in Galway. All data collection, including the baseline tests, the Croí MyAction intervention programme, and the one-year follow-up tests, occur in a community setting. Ethics approval for the study was obtained in March 2012 from the Clinical Research Ethics Committee of Galway University Hospital, part of Ireland’s Health Service Executive (HSE).

### Hypothesis

The formal null hypothesis to be tested in this study is that there is no difference in mean reduction in glucose dysfunction amongst the population of women with prior GDM following participation in Croí MyAction when compared with women receiving usual health care. The alternative hypothesis is that the Croí MyAction group will show significantly better outcomes than women receiving usual care.

### Sample size and power calculation

The sample size required for the RCT is 54 participants. This number was calculated based on estimates provided from pilot data from a group of women with a history of GDM (n = 74) receiving conventional health care. The pilot group had a standard deviation of 0.64 mmol/l for the difference in fasting plasma glucose (FPG) on an oral glucose tolerance test between two time points: approximately three months post-pregnancy and then one to three years later. Given the standard deviation, it is estimated that a sample size of 27 in each study arm is necessary to have 80% power to detect a mean difference of 0.5 mmol/l in FPG between baseline and one-year follow-up in the two study arms, using a two-sample t-test at the 0.05 significance level.

### Participants: recruitment and eligibility

Potential participants are identified from the Atlantic Diabetes in Pregnancy (DIP) research database and the pregnancy service of the Diabetes Day Centre at the University Hospital Galway. These women are sent invitation letters and research study information leaflets in the post. The mail-outs are then followed by phone calls from the study researchers to determine interest in the study (that is, obtain verbal consent), answer any questions about the study, and schedule appointments for baseline health assessments over the following month. On the baseline assessment days, the researchers obtain written, informed consent from each participant and administer a series of clinical, anthropometric, behavioural and psychological tests, measures and surveys, as described in Table 1 on the secondary outcome measures of the trial. The recruitment process is anticipated to span 10 months, from June 2012 to March 2013. The flow chart in Figure 1 represents the movement of a participant through the stages of recruitment to the study.

**Figure 1 F1:**
[figure not shown]
Participant flow through recruitment process.

**Table 1 T1:** Secondary outcomes: definitions and measurement techniques

	**Outcome**	**Definition and measurement**	**Timepoint measured**		
			**Baseline**	**Post-intervention**	**1-year follow-up**
1	Postprandial glucose dysfunction	Mean reduction in two-hour postprandial (PP) blood glucose on a 75 gram oral glucose tolerance test (OGTT)	✓		✓
2	Insulin resistance	Decrease in insulin resistance as measured by Homeostasis Model Assessment (HOMA) on insulin and glucose values on a 75 gram OGTT	✓		✓
3	Diet adherence	Two-point improvement in overall MedDietScore - a composite diet index based on the traditional Mediterranean dietary pattern	✓	✓	✓
4	Weight and shape	a. Mean weight reduction (kilograms) in individuals with a Body Mass Index (BMI) of >30 kg/m2 at baseline; and	✓	✓	✓
		b. Mean reduction in waist circumference in individuals with a measurement of >88 cm at baseline			
5	Physical activity and fitness	a. Proportions meeting physical activity target of at least 30 minutes of moderate intensity aerobic activity on at least five days of the week; and	✓	✓	✓
		b. Change in functional capacity on an objective physical fitness test (Chester Step Test or six-minute walk test), estimated in metabolic equivalents (METs) or time on test			
6	Lipid profile	a. Proportions achieving a lipid target profile of the following values: total cholesterol <4.5 mmol/l, LDL cholesterol <2.5 mmol/l, triglycerides <1.69 mmol/l, HDL cholesterol >1.29 mmol/l; and	✓	✓	✓
		b. Mean reduction in total and LDL cholesterol			
7	Psychological evaluation (including: positive mental health; general health; quality of life; perceived social support; motivation to change; diabetes-related self-efficacy; depression, anxiety and stress)	a. Positive mental health: four-items from RAND SF-36 questionnaire addressing affective aspects of well-being and five-items from the Mental Health Index-5 (MHI-5) in the RAND SF-36 questionnaire on the occurrence and extent of non-specific psychological distress	✓		✓
		b. General health: Stand-alone measure of self-rated health included in the Irish Survey of Lifestyle, Attitudes and Nutrition (SLÁN), 2007 (originally from The Healthy Days Measures (HRQOL-4))			
		c. Quality of life: Single-item assessment included in SLÁN 2007 (originally from the World Health Organization’s Quality of Life Survey (WHO-QOL Group, 1998))			
		d. Perceived social support: Multidimensional Scale of Perceived Social Support from family, friends, and a significant other (Zimet, Dahlem, Zimet and Farley, 1988)			
		e. Motivation to change: Moore *et al.*’s (2011) scale developed for Australian randomised controlled trial on a lifestyle intervention programme to prevent type 2 diabetes (based on Prochaska *et al.*’s (1992) identification of various stages in relation to maintaining a healthier lifestyle)			
		f. Diabetes-related self-efficacy: 18-item assessment of confidence to engage in exercise and healthy eating under different ‘barrier’ conditions (Moore *et al.*, 2011)			
		g. Depression, anxiety and stress: 21-item Depression, Anxiety and Stress Scale (DASS-21)			

Following the baseline health assessments, eligibility for the study is determined on the following criteria:

#### Inclusion criteria

Participants are women of child-bearing age, 18 years and older, with a history of GDM. At the time of recruitment, they also show at least one of the following diabetes risk factors:

1. Impaired fasting glucose (fasting plasma glucose levels of >5.6 <7 mmol/l^a^); or

2. Impaired glucose tolerance (two-hour plasma glucose levels of >7.8 <11.1 mmol/l); or

3. Insulin resistance based on homeostasis model assessment (HOMA) plus two of the following risk factors: (a) blood pressure > 130/80 mmHG, (b) total cholesterol >4.5 mmol/l, (c) LDL cholesterol >2.5 mmol/l, (d) triglycerides >1.69 mmol/l, (e) HDL cholesterol >1.29 mmol/l, (f) obesity (defined as BMI >30), (g) waist circumference >88 cm.

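### Inclusion item 3(e) counts HDL above 1.29 mmol/l as a risk factor while Table 1 makes the same value the lipid target, which decides entry for one narrow group of women

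*Protocol article*

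**What the plan says.** The Inclusion criteria section of the protocol article requires a history of GDM and that, at recruitment, women meet this condition: "they also show at least one of the following diabetes risk factors". Three alternative routes follow, joined by 'or'. The first is "Impaired fasting glucose (fasting plasma glucose levels of >5.6 <7 mmol/l". The second is impaired glucose tolerance, defined on the two-hour value. The third is "Insulin resistance based on homeostasis model assessment (HOMA) plus two of the following risk factors", followed by seven items, (a) to (g).

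Four of the seven items are lipids. Three read "b) total cholesterol >4.5 mmol/l, (c) LDL cholesterol >2.5 mmol/l, (d) triglycerides >1.69 mmol/l". The list ends "e) HDL cholesterol >1.29 mmol/l, (f) obesity (defined as BMI >30), (g) waist circumference >88 cm".

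Table 1, row 6 (Lipid profile), item a, defines a secondary outcome on the same four lipids: "Proportions achieving a lipid target profile of the following values: total cholesterol <4.5 mmol/l, LDL cholesterol <2.5 mmol/l, triglycerides <1.69 mmol/l, HDL cholesterol >1.29 mmol/l".

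The abstract (Methods/Design) describes the 54 women as having "persistent post-partum glucose dysfunction (impaired glucose tolerance (IGT) or impaired fasting glucose (IFG)), are randomly assigned". It does not mention the third route.

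**The concern.** If a risk factor means missing the trial's own target, each lipid should carry opposite signs in the two places. HDL carries the same sign and the same cut-off in both. One HDL value therefore counts towards a woman's diabetes risk at entry and towards success at follow-up. The eligibility criteria are stated in full in the article as the rules applied after the baseline assessment, so this is not a detail left to a longer document.

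At stake is who may enter by the third route, and whether the published criterion matches what was done at screening. Until the two places agree, eligibility under criterion 3 cannot be audited and the enrolled population cannot be described exactly.

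**Working it through.** **Step 1. The two lists side by side** (mmol/l; Inclusion criteria item 3 and Table 1 row 6a):

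| Lipid | Risk factor at entry | Target | Direction reversed? |
|---|---|---|---|
| Total cholesterol | >4.5 | <4.5 | yes |
| LDL | >2.5 | <2.5 | yes |
| Triglycerides | >1.69 | <1.69 | yes |
| HDL | >1.29 | >1.29 | no |

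The only endnote to the criteria concerns the glucose thresholds. No other text accounts for the HDL entry.

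**Step 2. Whose eligibility depends on the sign.** Women with IFG or IGT qualify by the first or second route whatever their HDL. The remaining case is a woman with HOMA insulin resistance and neither IFG nor IGT. Let k be the number of the other six items she has, from 0 to 6. I read the rule as at least two of seven. Her count is k plus 1 if item (e) is met, and she enters if the count is 2 or more.

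| k | HDL | Count as printed | Entry as printed | Count if reversed | Entry if reversed |
|---|---|---|---|---|---|
| 0 | >1.29 | 1 | no | 0 | no |
| 0 | <1.29 | 0 | no | 1 | no |
| 1 | >1.29 | 2 | **yes** | 1 | **no** |
| 1 | <1.29 | 1 | **no** | 2 | **yes** |
| 2 to 6 | either | at least 2 | yes | at least 2 | yes |

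There are 7 × 2 = 14 combinations of k and HDL side. Two change, both at k = 1. A value of exactly 1.29 is left aside.

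**Step 3. Sample size.** The inputs, from Sample size and power calculation, are SD 0.64 mmol/l, difference 0.5 mmol/l, 80% power and significance level 0.05 (two-sided assumed, as the article does not say).

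- Normal approximation: n per arm = 2(z₀.₉₇₅ + z₀.₈₀)² × SD² / difference² = 2 × (1.960 + 0.842)² × 0.4096 / 0.25 = 25.7, so 26.
- Two-sample t-test: 26.7, so 27 per arm, with power 80.4% at 27.

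The stated 27 per arm reproduces. HDL enters none of these terms, so the figure is the same under either sign.

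**Step 4. The abstract.** Its population is IFG or IGT. Criterion 3 is a third alternative and needs neither. The two descriptions differ whichever HDL sign is used, so this is a separate discrepancy.

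**The case against.** The strongest reply is that item (e) looks like a misprint with a narrow reach. The other three lipids fit that reading, and nothing in the article shows which sign was used at screening. This stands. It cannot be said that women at HDL target were in fact enrolled, or that low-HDL women were in fact refused, only that the printed rule has that effect. A woman admitted this way would still have prior GDM, insulin resistance and one other listed factor.

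It can also be said that eligibility is settled before the 1:1 randomisation and that HDL plays no part in the primary outcome. That stands too: the error bears on who is enrolled and described, not on the comparison between arms. Recruitment was expected to finish by March 2013 and the article appeared on 2 May 2013, so a correction now mainly serves the record. That lowers the urgency but leaves the contradiction in place.

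Two stronger readings are tempting. A reader might infer that every woman assessed under criterion 3 is affected. Step 2 shows that only those with exactly one other factor are.

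A reader might also infer a loss of power, because women entering by criterion 3 alone have fasting glucose no higher than about 5.6 mmol/l and may have little room for a 0.5 mmol/l fall. That argument concerns the existence of criterion 3, not the HDL sign. A low-HDL woman admitted under the reversed sign would have equally low fasting glucose, so changing the sign would recover nothing. A woman entering by IGT alone can be in the same position, and the abstract includes her. The article gives no share of such women and no ground for assuming that they have no effect.

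**Conclusion.** The contradiction between item 3(e) and Table 1 row 6a is plain on the face of the document and needs no outside source. Its reach is one group: insulin-resistant women with neither IFG nor IGT and exactly one other listed factor. In that group, the printed rule admits those at the HDL target and refuses those below it.

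The size of the group cannot be computed, because the article gives neither an HDL distribution nor the share of women entering by criterion 3. Sample size, stated power and the validity of the randomised comparison are untouched. The conclusion assumes that the rule means at least two of the seven items and that it was applied as printed, which only the sponsor can confirm.

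The mismatch between the abstract's population and criterion 3 is also real. It is a separate point and adds no weight to this one.

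**What to change.** 1. Reconcile item 3(e) with Table 1 row 6a, and state which HDL sign has been applied at screening since enrolment opened on 14 June 2012.
2. Re-check the screening records of women assessed under criterion 3.
3. Keep all randomised women in the intention-to-treat set. If the printed sign was applied, report how many entered only through 3(e).
4. Separately, align the abstract's population with the inclusion criteria, so that it covers women who enter by criterion 3 with neither IFG nor IGT.

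The cost is a correction to one item, a review of existing screening sheets, at most one reported count, and a changed phrase in the abstract. No new data are needed, and the sample size stays as it is.
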